### Study design

Prior to the primary intervention, all selected individuals will participate in a two-week "run-in" period during which relevant questionnaires are used to gather information regarding sociodemographic variables, the history of diseases, drug and supplement use, dietary intakes, and physical activity levels. At the end of the run-in period and before the start of the intervention, people will be randomly assigned to the intervention and control groups. A computerized randomization will be carried out using a block randomization procedure of size 2 and 4, stratified by gender (male or female), and BMI (25–30 or 30–35 kg/m^2^). Each patient will get an identity number, which will be input into the computer's randomization program together with the codes of patients who have the same age and BMI. The intervention or control groups will ultimately be randomly allocated to patients with the same conditions. Random allocation will be performed by a person unaffiliated with the study. Subjects in the intervention group will consume 300 g of synbiotic yogurt and those in the control group will consume 300 g of regular yogurt daily for 12 weeks (Fig. 1). Participants will be asked not to change their regular physical activity and usual dietary intakes during the study. They will also be asked not to use any other probiotic or synbiotic products while participating in the trial. The participants' dietary intake will be evaluated again at the end of the sixth week as well as at the end of the trial in order to evaluate the patients' nutritional intake during the study and to ensure yogurt consumption. Physical activity level will also be assessed during the sixth week and the last week. Blood samples (10 cc) will be obtained after a 12-h overnight fast at baseline and at week 12 for biochemical measurements (Table 1).

**Fig. 1 Fig1:**
[figure not shown]
Template of content for the schedule of enrolment, interventions, and assessments

**Table 1 Tab1:** Product delivery program and follow up participants

Visit time	Run in week -2(day-14)	meeting day (day 0)	Week 2 (day 14)	Week 4 (day 28)	Week 6 (day 42)	Week 8 (day 56)	Week 10 (day 70)	Week 12 (day 84)	Week 13 (day 91)
**Delivery of yogurt**		*	*	*	*	*	*	*	
**Anthropometric measurements**		*						*	
**Blood pressure measurement**		*						*	
**Blood sampling**		*						*	
**record 24-h food recall**	*	*			*			*	
**Assessment of physical activity**	*	*			*			*	
**End of intervention**								*	
**Evaluation of adverse events**		*	*	*	*	*	*	*	*

### The intervention

The synbiotic yogurt that will be used in this study contains strains of Lactobacillus plantarum, Lactobacillus pentosus (2˟10^8^ CFU), Chloromyces marcosianos yeast, and 3% of various natural plants (celery, shallot, chicory, and mint). The colony rate of both bacterial strains was reported as 2˟10^8^ by microbiological analysis; however, before the intervention, yogurt quality control will be carried out under the supervision of the Food and Drug Administration laboratory in Yasuj, Iran, to confirm the presence of this colony rate. The maximum degree of similarity will be observed in both yogurts, and there will be no labels on the containers to blind both the researchers and subjects to the type of the yogurt they received. In the case of a serious adverse event, patients are unmasked to ensure their safety. In these circumstances, unblinding is carried out using a set of operationalized guidelines by an unblinded medical assessor who has access to randomization while not actively participating in the trial. For each participant, the amount of yogurt required to consume during two weeks will be packed and delivered every two weeks. Participants will be asked to keep the yogurt bottles in the refrigerator. To remind them to consume yogurt, they will receive weekly calls and short messages. Compliance with the consumption of yogurt will be monitored by counting the number of returned unused and used yogurt containers every two weeks. Evaluating the consumption of the yogurts will also be done through food recalls.

### Anthropometric measurements

Anthropometric parameters, including weight, height, BMI, and WC, will be measured for all participants at baseline and at the end of the study. A digital scale with a 100-g precision will be used to measure the subject's weight while wearing light clothing and no shoes. The standing height of people will be measured using a standard height meter without shoes and with an accuracy of 0.5 cm. WC will be measured using a tape measure in the middle of the distance between the superiliac bone and the last rib with an accuracy of 0.5 cm. Then the BMI will be calculated by dividing the weight (kg) by the squared of the height (m).

### Assessment of dietary intakes and physical activity level

A 24-h dietary recall questionnaire will be used to assess the daily dietary intakes of the study subjects during two weekdays and one weekend day at baseline, at the end of the sixth week, and at the end of the trial. Nutritionist IV software will be used to determine participants' macronutrients and micronutrients intakes using the data obtained from food recalls.

Physical activity level will be evaluated at baseline, during the sixth week, and at the last week using the international physical activity questionnaire (IPAQ), which has been validated for the Iranian population [22]. Physical activity level in terms of MET-h/wk will be calculated according to the activity performed using the standard MET table and will be classified into three levels including low, moderate, and high intensity physical activity.

### Blood pressure measurement

The subjects' systolic and diastolic blood pressure will be measured twice with a 15-min interval in the left arm using a mercury barometer in a sitting position after a 10-min rest. Subjects will be asked to avoid smoking, drinking coffee, or heavy exercise for 30 min before the measurement. The average of the two measurements will be used to figure out the blood pressure.

### Biochemical assessment

Venous blood samples (10 cc) will be collected after 10 –12 h of fasting at the beginning and end of the study. The serum samples will be separated from whole blood (9 cc) by centrifugation at 3500 rpm for 10 min. The remaining 1 cc of whole blood samples will be stabilized in EDTA tubes. Both serum and whole blood samples will be immediately transferred to the freezer at -70 °C until the tests are performed. Serum TG and HDL-C concentrations will be measured using standard kits and enzymatic methods. Plasma atherogenic index (AIP) will be calculated through the formula AIP = logTG/HDL. Circulatory ox-LDL will be measured using the ELISA method and the relevant commercial kit using the autoanalyzer. Serum concentrations of Apolipoprotein A1 (ApoA1) and Apolipoprotein B (ApoB) values ​​will be assessed using the immunoturbidometry method. The concentration of serum malondialdehyde (MDA) will be determined based on the reaction with thiobarbituric acid (TBA) and using the spectrophotometric method. The serum values ​​of Total Antioxidant Capacity (TAC), Total Oxidant Status (TOS), Superoxide Dismutase (SOD), and Glutathione Peroxidase (GPx) will be measured using commercial kits and by spectrophotometric method. FBS will be measured on the same day of sampling using the glucose oxidase enzyme method. Insulin concentration will be measured by the ELISA method. Homeostatic Model Assessment for Insulin Resistance (HOMA-IR) will be calculated through the following formula: HOMA-IR = (FBS (mg/dl) x fasting insulin (μu/ml))/405.

### Adverse event reporting

The research executive team will be informed of any adverse side effects and will keep a record of any adverse incidents.

### Patient and public involvement

Patients or the public were not involved in the design, conduct, reporting, or dissemination plans of this research.

### Statistical methods

Data will be analyzed using SPSS software version 23. The normality of the distribution of the variables will be checked by the Kolmogorov–Smirnov test. All normal distributed quantitative data will be reported as mean ± standard deviation, and qualitative data will be reported as frequency (percentage). Analyses of non-normal variables will be performed after logarithmic transformation. Comparisons of baseline characteristics will be performed using independent t-test (for quantitative data) and chi-squared test (for qualitative data). Analysis of covariance (ANCOVA) test will be used to compare the effect of the intervention between the two groups by adjusting baseline values and confounding variables. A paired t-test will be used for within group comparisons. P < 0.05 will be considered to be statistically significant.

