## Abstract

**Background:**

Metabolic syndrome is recognized as one of the most common global health issues, which may cause numerous side effects. Studies have shown the favorable effects of probiotic supplements on glycemic indices, lipid profiles, and oxidative stress status. However, the number of studies investigating the effects of food products containing probiotics and prebiotics on metabolic diseases is limited. Limited evidence also shows that products containing Lactobacillus plantarum could affect metabolic alterations in chronic diseases. No previous study evaluated the impact of synbiotic yogurt containing Lactobacillus plantarum on people with metabolic syndrome. Therefore, the current study aims to investigate the effect of the newly developed synbiotic yogurt containing Lactobacillus plantarum, Lactobacillus pentosus, and Chloromyces marcosianos yeast on the components of metabolic syndrome, oxidative stress status, and some other risk factors for cardiovascular diseases in adults with metabolic syndrome.

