### Sample size calculation

Sample size was calculated using the following formula, with inputs including the mean and standard deviation of TG changes in the intervention (212.8 ± 21.1) and control (201.9 ± 19.6) groups obtained from the Cicero et al. study [21], 95% confidence, and 80% power of the test. The minimum sample size in each group was calculated to be 17 cases. However, after adjusting for possible dropouts, this number increased to 22 cases in each group.

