## Discussion

In recent years, the prevalence of MetS has significantly increased [23]. The pathophysiology of MetS is significantly influenced by oxidative stress, inflammation, and insulin resistance [24]. Studies show that dysbiosis may play a major role in the development and progression of these variables [25]. Probiotics can alter the gut bacteria to reduce the risk factors for metabolic syndrome [26]. The number of research examining the benefits of probiotic supplements is substantial, however there are few studies examining the effects of probiotic and prebiotic food products in metabolic diseases. However, no study has been conducted to evaluate the effect of synbiotic yogurt containing Lactobacillus plantarum, Lactobacillus pentosus, and Chloromyces marcosinos yeast in people with metabolic syndrome. In the present study, our aim is to investigate the effect of consumption of newly developed synbiotic yogurt containing Lactobacillus plantarum, Lactobacillus pentosus, and Chloromyces marcosianos on metabolic components, oxidative stress status, and some other cardiovascular disease risk factors in adults with MetS. If the appropriate impact of synbiotic yogurts on the outcome variables is identified in the current study, including these items in the dietary management of patients with MetS will be a cost-effective method of using probiotics.

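### The trial is sized on triglycerides but names no primary outcome, so its main claim has no 5% error control across about 19 outcomes

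*Protocol article*

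**What the plan says.** The aim in the protocol article's Abstract is to study the yogurt's effect "on the components of metabolic syndrome, oxidative stress status, and some other risk factors for cardiovascular diseases in adults with metabolic syndrome". That is three families of outcomes, unranked. The Introduction and Discussion repeat them, and no section calls any outcome primary or secondary.

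TG is singled out only under Sample size calculation, where the inputs are the "mean and standard deviation of TG changes" taken from a cited study.

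Under Statistical methods, an ANCOVA "test will be used to compare the effect of the intervention between the two groups by adjusting baseline values and confounding variables", with no outcome named. The section adds: "A paired t-test will be used for within group comparisons". It closes with a single threshold: "P < 0.05 will be considered to be statistically significant".

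The Discussion links use of the product in dietary management to a condition that names no outcome: "If the appropriate impact of synbiotic yogurts on the outcome variables is identified in the current study".

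**The concern.** The sample size and the main conclusion both depend on which outcome is primary. Here TG determines the number of participants, but neither the analysis nor the conclusion gives it any special standing. A report that followed this text could rest its main claim on whichever outcomes fell below 0.05.

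The nominal 5% would then apply to each test separately and not to the statement that the yogurt works. A chance finding on one biomarker could become the headline of a trial of 44 people and be carried into dietary advice.

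**Working it through.** **Inputs from the protocol article**

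- Anthropometric measurements ("weight, height, BMI, and WC, will be measured for all participants at baseline and at the end of the study"): weight, BMI and WC. Height is not an outcome in adults. Count: 3.
- Blood pressure measurement ("systolic and diastolic blood pressure will be measured twice with a 15-min interval"): systolic and diastolic. Count: 2.
- Biochemical assessment: TG, HDL-C, AIP, ox-LDL, ApoA1, ApoB, MDA, TAC, TOS, SOD, GPx, FBS, insulin, HOMA-IR. Count: 14.
- Total: 3 + 2 + 14 = 19.
- Threshold 0.05 for each. Sidedness is not stated; two-sided is assumed.
- The article gives no correlations between outcomes, so those below are assumptions.

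**Step 1. The plan's own figure: 17 per group**

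n = (1.960 + 0.842)² × (SD₁² + SD₂²) / difference²

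Difference = 212.8 − 201.9 = 10.9; SDs 21.1 and 19.6.

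n = 7.849 × (445.21 + 384.16) / 118.81 = 54.8, so 55 per group.

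The stated 17 does not reproduce. A one-sided test gives 44. Baseline adjustment would bring 55 down to about 17 only with a baseline correlation near 0.83, since 55 × (1 − 0.83²) = 17.1, and no such correlation is stated. Unadjusted power on these inputs (normal approximation) is about 34% at 17 per group and 43% at 22. This does not enter the error rates below, but it matters for the remedy.

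**Step 2. Any significant between-group result, either direction, no true effect**

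Independent tests: 1 − 0.95^19 = 62%.

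Independence cannot hold, because AIP is calculated from TG and HDL, HOMA-IR from FBS and insulin, and BMI from weight. Dropping those three gives 1 − 0.95^16 = 56%.

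**Step 3. At least one significant result in the favourable direction**

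Each two-sided 5% test has a 2.5% chance of a favourable false positive. Independent tests: 1 − 0.975^19 = 38%.

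**Step 4. Assumed common correlation across all 19**

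Simulated null z tests, with every outcome scored so that favourable is positive:

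| Correlation | Either direction | Favourable |
|---|---|---|
| 0 | 62% | 38% |
| 0.2 | 57% | 31% |
| 0.3 | 53% | 27% |
| 0.5 | 41% | 20% |

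A second model builds in the three dependences from Step 2 and adds a background correlation among the other outcomes. For either direction it gives 54% to 57% at background 0, 50% to 53% at 0.2, 46% to 48% at 0.3, and about 37% at 0.5.

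**Step 5. Comparison**

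One pre-named outcome at two-sided 5% gives 5% in either direction and 2.5% in the favourable direction. The paired within-group tests, up to 2 × 19 = 38 more, are not in any of these figures.

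**The case against.** Four points deserve a fair hearing.

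*A false-positive claim is not shown to be more likely than not.* A reader might infer this from the 62%. The documents do not support it. That figure needs 19 independent tests, and passing 50% takes the equivalent of at least 14 (1 − 0.95^13 = 49%; 1 − 0.95^14 = 51%). It also counts unfavourable chance results, which cannot support a claim of benefit. For favourable results the figure stays below 50% in every scenario examined. This objection stands.

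*The Discussion sets no decision rule.* A reader might infer that any one significant outcome would suffice. The sentence speaks of outcome variables in the plural and does not say so. That also stands. However, nothing in the text rules the reading out, because neither the outcomes nor the effect required are specified.

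*The count of 19 is a reading of the measurement sections.* Statistical methods does not list the variables to be analysed, and weight and BMI are not metabolic syndrome criteria. This is fair, hence about 19. A narrower count does not remove the problem: the six component measures alone (WC, systolic and diastolic pressure, TG, HDL, FBS) give 1 − 0.95^6 = 26% in either direction and 1 − 0.975^6 = 14% favourable, if independent.

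*Multiplicity methods may sit in an analysis plan that is not shown.* True, and the absence of a named adjustment for secondary outcomes is no part of this point. The point is that this document sizes the trial on one outcome, then fixes a significance rule and a conclusion that do not single it out.

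**Conclusion.** The point holds in this form: TG is the sizing variable but not a declared primary outcome, and the threshold and conclusion as written leave the main claim without 5% error control.

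If the yogurt has no effect, the chance of some between-group P below 0.05 is 62% under independence and roughly 37% to 57% under the assumed correlations, against 5%. The chance of a favourable one is about 38% under independence and about 20% to 31% at correlations of 0.5 to 0.2, against 2.5%. On the favourable measure that is about 8 to 15 times the rate for one pre-named outcome (20 / 2.5 = 8; 38 / 2.5 = 15).

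These sizes rest on the count of 19, two-sided testing and correlations that the documents do not give. The absence of a declared primary outcome rests on none of them.

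**What to change.** Before analysis:

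1. Declare the baseline-adjusted between-group difference in TG at week 12 as the single primary outcome, tested at two-sided 5%. TG is proposed because the trial was sized on it.
2. Label the remaining outcomes secondary or exploratory, and report each with an estimate and 95% confidence interval.
3. Reword the Discussion's conditional sentence so that the conclusion depends on the primary outcome.
4. Restate Sample size calculation together with item 1. Either give the inputs and formula that lead to 17, including any baseline correlation relied on, or correct the number. Without this, the trial would be tied to an outcome for which its printed inputs give about 43% unadjusted power at 22 per group.

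Items 1 to 3 take a few sentences. The price is that isolated secondary P values can no longer be claimed as effects. Item 4 may cost more: if the inputs stand as printed, the sponsor must enlarge the trial, justify a smaller variance through baseline adjustment, or state openly that power for TG is low.

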## Discussion

In recent years, the prevalence of MetS has significantly increased [23]. The pathophysiology of MetS is significantly influenced by oxidative stress, inflammation, and insulin resistance [24]. Studies show that dysbiosis may play a major role in the development and progression of these variables [25]. Probiotics can alter the gut bacteria to reduce the risk factors for metabolic syndrome [26]. The number of research examining the benefits of probiotic supplements is substantial, however there are few studies examining the effects of probiotic and prebiotic food products in metabolic diseases. However, no study has been conducted to evaluate the effect of synbiotic yogurt containing Lactobacillus plantarum, Lactobacillus pentosus, and Chloromyces marcosinos yeast in people with metabolic syndrome. In the present study, our aim is to investigate the effect of consumption of newly developed synbiotic yogurt containing Lactobacillus plantarum, Lactobacillus pentosus, and Chloromyces marcosianos on metabolic components, oxidative stress status, and some other cardiovascular disease risk factors in adults with MetS. If the appropriate impact of synbiotic yogurts on the outcome variables is identified in the current study, including these items in the dietary management of patients with MetS will be a cost-effective method of using probiotics.

## Data Availability

Not applicable.

## Abbreviations

MetS: Metabolic syndrome
NCEP: National Cholesterol Education Program
ROS: Reactive oxygen species
LDL: Low-density lipoprotein
Ox-LDL: Oxidized low-density lipoprotein
NO: Nitric oxide
MDA: Malondialdehyde
BMI: Body mass index
WC: Waist circumference
TG: Triglyceride
HDL: High-density lipoprotein
FBS: Fasting blood sugar
IPAQ: International Physical Activity Questionnaire
AIP: Plasma atherogenic index
ApoA1: Apolipoprotein A1
ApoB: Apolipoprotein B
TBA: Thiobarbituric acid
TAC: Total Antioxidant Capacity
TOS: Total Oxidant Status
SOD: Superoxide Dismutase
GPx: Glutathione Peroxidase
HOMA-IR: Homeostatic Model Assessment for Insulin Resistance
